## Abstract

**Background:**

Postoperative pulmonary complications (PPCs) are severe and are of particular concern in older adult patients undergoing laparoscopic gastrointestinal surgery. Both 40% and 80% fraction of inspired oxygen (FiO_2_) are commonly used for anesthesia. Presently, whether 40% FiO_2_ can increase the oxygenation index of patients 48 h postoperatively and reduce PPCs remains controversial. Moreover, no clear consensus exists for older adult patients. Therefore, this study aims to compare the effects of low FiO_2_ (40%) and high FiO_2_ (80%) levels on postoperative pulmonary function in older adult study participants undergoing laparoscopic gastrointestinal surgery.

**Methods:**

This multicenter, prospective, parallel-cohort, randomized controlled clinical trial will include 1098 older adult participants aged ≥ 65 years old undergoing laparoscopic gastrointestinal surgery, from 16 clinical trial sites across China. Participants will be randomized, as per a 1:1 ratio to two cohorts, the “L” and “H” cohorts, to receive low FiO_2_ (40%) and high FiO_2_ (80%) levels, respectively. The primary outcome measure is the 48-h postoperative oxygenation index between the two cohorts. The secondary outcome measures include the other blood gas analysis results, PPCs within 7 days, and 30-day mortality rate.

**Discussion:**

This study of elderly patients undergoing laparoscopic gastrointestinal surgery with different intraoperative oxygen concentrations at high risk for pulmonary complications. All subjects were followed up for up to 30 days for pulmonary function, postoperative complications, etc. Randomization was performed separately at 16 sites.

**Trial registration:**

ClinicalTrials.gov NCT06359106. Registered and posted on April 11, 2024.

**Supplementary Information:**

The online version contains supplementary material available at 10.1186/s13063-026-09471-3.

## Introduction

### Background and rationale {6a}

The World Health Organization (WHO) and United States Center for Disease Control recommend the use of 80% oxygen in the perioperative period, to reduce surgical site infections after general anesthesia [1, 2]. Moreover, clinical anesthesiologists use pure oxygen during the induction and awakening phases of general anesthesia to prevent hypoxemia, particularly in patients with a risk of difficult airways and critical illnesses [3, 4].

However, controversy exists regarding the safety of the perioperative use of a high fraction of inspired oxygen (FiO_2_). With a difficult airway, 100% FiO_2_ is usually administered during a short period, due to the risk of prolonged apnea. In particular, this short inhalation of pure oxygen causes absorption atelectasis in 90% of patients [5, 6], which may be present postoperatively [7, 8]. Absorption atelectasis results in reduced lung compliance, oxygen damage, and impaired oxygen delivery and lung function. The results of a meta-analysis have revealed an association between decreased oxygen levels and parameters and increased atelectasis severity, after high FiO_2_ during anesthesia [9, 10].

Postoperative atelectasis is an important risk factor for postoperative pulmonary complications (PPCs), such as pneumonia, resulting in increased postoperative morbidity and mortality rates and prolonged hospital stays [11–13]. Therefore, PPCs are severe and are of particular concern in older adult patients undergoing laparoscopic gastrointestinal surgery.

A study involving 73,992 participants found that a high FiO_2_ increases PPCs and the 30-day postoperative mortality rate [14].

Moreover, further studies have uncovered that in acute and severe cases, the administration of high concentrations of FiO_2_ does not improve important clinical outcomes and results in an increased mortality rate [15].

Conversely, the findings of a few meta-analyses have revealed that the use of high FiO_2_ during general anesthesia does not increase postoperative mortality, intensive care unit (ICU) occupancy, pneumonia, and atelectasis [16, 17]. Furthermore, the results of a controlled intervention trial comprising 5749 patients have revealed the absence of an effect of high FiO_2_ levels on 30-day mortality rates or wound healing [18, 19].

Excessive oxygen directly results in toxic effects involving the lung [20]. Furthermore, excessive oxygen induces vasoconstriction, inflammatory responses, and oxidative stress, impacting on the pulmonary, cardiovascular, and nervous systems [21, 22]. Moreover, a high FiO_2_ administered during surgery lacks evidence regarding the benefits thereof for postoperative infection [23].

PPCs frequently occur post-lung resection and have a considerable impact on postoperative morbidity and mortality. The prevalence of PPCs post-lung resection, which ranges from 14 to 59%, is notably higher than that of other major surgeries that do not require single-lung ventilation [24–27].

Thus, employing a ventilation strategy that protects the lungs can decrease the incidence of PPCs [28, 29]. Due to the inconsistency of evidence, the 2019 International Expert Development Consensus on Lung-Protective Ventilation has not recommended any specific mode of ventilation [29].

Pressure-controlled ventilation (PCV) results in better oxygen and inspiratory pressure supply, an improved lung compliance, and a reduced release of inflammatory mediators, in patients undergoing thoracic and abdominal surgery [30–43].

However, an analysis involving 109,360 patients revealed a notable increase in PPCs in the PCV group than that in the volume-controlled ventilation (VCV) group [38]. As has been recommended for intraoperative use, for reducing airway pressure and improving oxygenation, the PCV-volume guaranteed ventilation (VG) mode is preferred, based on the characteristics of PCV and VCV [37–39]. Nonetheless, no conclusive evidence exists indicating that any mode of ventilation can reduce the incidence of PPCs.

Current evidence supports low FiO_2_ for positive clinical outcomes; however, the latest guidelines recommend an intraoperative FiO_2_ with a lower limit of 40% [43]. The WHO Guidelines Development Group suggests that the FiO_2_ in patients undergoing endotracheal intubation under general anesthesia should be 80%, to reduce the incidence of postoperative atelectasis [44].

Moreover, FiO_2_ is generally set at 30% to 100% in clinical practice. Recommendations include adding air to the inhaled gas and adjusting the FiO_2_ from 30 to 40%.

Therefore, both 40% and 80% FiO_2_ are commonly used for anesthesia. Presently, whether 40% FiO_2_ can increase the oxygenation index of patients 48 h postoperatively and reduce PPCs remains controversial. Moreover, at present, no consensus exists regarding the best intraoperative FiO_2_ to be used for lung function under anesthesia, whether spontaneous breathing or endotracheal intubation is employed. No clear consensus exists for older adult patients.

This multicenter, prospective, parallel-cohort, randomized controlled clinical study aims to compare the effects of low FiO2 (40%) and high FiO2 (80%) levels on postoperative pulmonary function in older adult participants undergoing laparoscopic gastrointestinal surgery.

### Objectives {7}

#### Primary objective

To investigate whether varying levels of intraoperative FiO_2_ affect the 48-h postoperative oxygenation index in older adult participants who have undergone laparoscopic gastrointestinal surgery.

#### Secondary objectives

To compare the results of blood gas analyses including PH value and PaCO_2_ lactic acid between the two cohorts, within 48 h postoperatively.To compare the time of oxygen inhalation, the inspired oxygen concentration, and the rate of oxygen uptakeTo compare the 7-day pulmonary and 30-day mortality rate between the two cohorts

#### Trial design {8}

The planned study is a multicenter, prospective, parallel-cohort, randomized controlled clinical trial, and the start date is 2 July 2024, with an estimated end date of 31 December 31, 2025. Figure 1 illustrates the trial design.

**Fig. 1 Fig1:**
[figure not shown]
Trial flowchart

### Eligibility criteria {10}

The inclusion criteria are as follows:Participants aged ≥ 65 years oldParticipants with Grades I–III, as per the American Society of Anesthesiologists (ASA) Physical Status Classification System.Participants without a previous history of drug allergies or abnormal reactions to anesthesiaParticipants with an operative time > 2 hParticipants undergoing laparoscopic gastrointestinal surgeryParticipants with a preoperative oxygen saturation not < 94%Participants for whom extubation is planned in the operating room

The exclusion criteria are as follows:Patients who have experienced acute lung injury or acute respiratory distress syndrome in the past 3 monthsPatients with a cardiac function class IV, as per the New York Heart Association classificationPatients with chronic renal failure, as evidenced by an estimated glomerular filtration rate of 30 mL/min/1.73 m^2^Patients with severe hepatic diseasePatients with blurred consciousness or cognitive dysfunctionPatients with severe coagulation dysfunctionPatients without a measurement of preoperative oxygen inhalationPatients with blood oxygen level < 94%Patients with severe pulmonary dysfunction Patients intubated with an endotracheal tube who are admitted to ICU, postoperatively Patients with a body mass index > 30 kg/m^2^

The rejection criteria are as follows:Participants who could not complete the studyParticipants with life-threatening cardiovascular and cerebrovascular events occurring intraoperativelyThe operation involves the thoracic cavity or is converted to open surgery.The surgical procedure lasts > 8 h.The amount of bleeding is > 800 ml.

The intervention will be handled by an experienced anesthesiologist. Prior to study initiation, researchers will receive training on the study protocol, according to the principles of GCP for clinical trials.

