### Withdrawal from study

Participants will be withdrawn from the study, if any of the following circumstances arise:The participant has voluntarily withdrawn consent from the study.Continuing in the trial will may be harmful to the health of the participant.The trial records cannot be completed, and the research investigator regards the participant as no longer able being to continue in the trial.AEs related to the trial intervention occur.Factors posing a risk are considered by the Trial or Advisory Committee.The rationale for a participant’s withdrawal from the study will be documented in the “Withdrawal/Change of Status” table.

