## Assignment of interventions: allocation

### Sequence generation {16a}

Post-initiation of the study, each clinical trial site will continuously screen eligible participants and enroll them in the trial. Participants will be randomly assigned. The study employed block randomization with center stratification, where each center competed for inclusion. The electronic data capture (EDC) system generated the randomization. The participants will be assigned to two cohorts, as per a 1:1 ratio, on the preoperative day. To balance the variables, we will stratify the participants according to the following factors: age, surgical position, area of the clinical trial site, operative time, and the anesthetic drug administration and method.

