### Methods for additional analyses (e.g., subgroup analyses) {20b}

#### Analysis sets

The enrolled set will consist of all participants who provided informed consent and were added to the study database.The full analysis set (FAS) describes the analysis set, which is as complete and close as possible to the intention-to-treat ideal of including all randomized participants, who have undergone ≥ 1 efficacy assessment, post-randomization.The per-protocol set (PPS) defines a subset of the participants in the FAS who are more compliant with the protocol and have undergone ≥ 1 efficacy assessment, post-randomization. Participants with protocol deviations will be excluded from this analysis.

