### Methods in analysis to handle protocol nonadherence and any statistical methods to handle missing data {20c}

In the analysis of the primary outcome measure, missing values within the FAS will be excluded.

The analysis of the primary, secondary, and safety outcome measures will be conducted, based on the intention-to-treat principle. Thus, participants will be analyzed, according to either of the intervention cohorts to which they were randomized, and all participants will be included in the analysis, regardless of whether they were assigned to the intervention or not (the FAS).

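### Rejection and withdrawal after randomisation, and dropped missing values, conflict with the stated intention-to-treat analysis of all participants

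*Protocol article*

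**What the plan says.** All references are to the Protocol article.

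- Timing (Sequence generation {16a}): "The participants will be assigned to two cohorts, as per a 1:1 ratio, on the preoperative day".
- Rejection list (Eligibility criteria {10}): non-completion of the study, a life-threatening cardiovascular or cerebrovascular event during surgery, thoracic involvement or conversion to open surgery, surgery longer than 8 h, and "The amount of bleeding is > 800 ml". The term rejection is not defined.
- Withdrawal from study: one of the grounds is "AEs related to the trial intervention occur".
- Analysis sets: the FAS is described as close to the intention-to-treat ideal but is limited to randomised participants "who have undergone ≥ 1 efficacy assessment, post-randomization". The PPS drops participants with protocol deviations; the rejection list is not mentioned there.
- Section {20c}: "In the analysis of the primary outcome measure, missing values within the FAS will be excluded". The same section applies intention to treat to primary, secondary and safety outcomes and says "all participants will be included in the analysis, regardless of whether they were assigned to the intervention or not".
- The Abstract (Discussion) adds that all subjects are followed for up to 30 days.

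Two eligibility items also sound like later events: the exclusion "Patients intubated with an endotracheal tube who are admitted to ICU, postoperatively" and an inclusion criterion of operative time over 2 h.

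**The concern.** Every item on the rejection list, and an intervention-related AE, arises after the participant has been randomised. If such participants leave the analysis, the compared groups are no longer those that randomisation produced.

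The items differ in how much this matters. Not completing the study, an AE caused by the intervention and a missing 48-h blood gas plausibly relate to oxygenation, pulmonary complications and death, which are the trial's outcomes. Conversion, bleeding and long surgery are mainly surgical events and less plausibly driven by FiO2, although the anaesthesiologists are not blinded.

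At stake is who enters the primary analysis. As the text stands, two analysts could each follow it and analyse different participants.

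**Working it through.** **Step 1. Apply the rules to three participants.**

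- Converted to open surgery, 48-h gas available. The rejection list points to removal. The FAS definition and the intention-to-treat statement both keep the participant in.
- Withdrawn for an intervention-related AE before the 48-h sample. The withdrawal section takes the participant out of the study. A PACU or 24-h record might satisfy the FAS condition, but the primary value is missing and is dropped. The intention-to-treat statement includes the participant.
- Does not complete and has no efficacy assessment. Rejected, outside the FAS and without a primary value, yet covered by the statement that everyone is included.

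In each case at least two statements give opposite answers. No section says that rejected or withdrawn participants are still followed and kept in the FAS.

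**Step 2. Reproduce the sample size (Sample size {14}).** Inputs: means 384 and 340 mmHg, margin 30 mmHg, SD 74 mmHg, one-sided α 0.025, power 80%, dropout 20%.

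- Assumed difference beyond the margin: (384 − 340) − 30 = 14 mmHg.
- Per arm: n = 2 × (1.960 + 0.842)² × 74² / 14² ≈ 439, as stated.
- With dropout: 439 / 0.80 = 548.75, so 549 per arm and 1098 in total, as stated.
- SE of the difference at 439 per arm: 74 × √(2/439) = 5.0 mmHg.

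The sample size is not in error. Its allowance is 549 − 439 = 110 per arm, 220 in total. It protects power (80.1% at 20% loss, against 88.0% if all 549 per arm are analysed) but does not protect against bias.

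**Step 3. Illustrate the bias.** If a fraction r of an arm is removed, and those removed average D mmHg below the full arm mean, the retained mean rises by D × r/(1 − r). The bias in the difference is this term in one arm minus the same term in the other. The documents give neither r nor D, so all values below are assumed.

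- 5% versus 0%, D = 100: 100 × 0.05/0.95 = 5.3 mmHg. With D = 60: 3.2 mmHg.
- 22.5% versus 17.5% (around the planned 20% loss), D = 100: 100 × (0.225/0.775 − 0.175/0.825) = 100 × (0.2903 − 0.2121) = 7.8 mmHg.
- 22% versus 18%, D = 50 to 100: 3.1 to 6.3 mmHg. If more are removed from the 40% arm, the one-sided error at the 30 mmHg margin rises from 0.025 to between 0.09 and 0.24. If more are removed from the 80% arm, power falls from 80% to between 59% and 34%.
- 20% versus 20%, same D: zero.

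**The case against.** The best defence has four parts.

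**Eligibility is settled before surgery.** Recruitment {15} says the inclusion and exclusion criteria are applied at preoperative visits. A reader might take the ICU line as removing patients who in fact stay intubated, especially since "Participants for whom extubation is planned in the operating room" already covers the planned case. The documents do not support that. The saturation limit of 94% also appears as both an inclusion and an exclusion criterion, so mirrored items are this article's habit, and Intervention description {11a} provides for participants still intubated in the PACU. The ICU and 2 h items most likely mean planned and expected. This part stands, and reduces both items to wording.

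**Rejection may not mean removal from analysis.** The term is undefined, the PPS offers a place for such cases, and {20c} states intention to treat. A reader might also infer that withdrawal ends outcome collection, or that complications and deaths drop out of the secondary outcomes. The withdrawal section does not say the former, {22} continues AE follow-up to resolution, and {20c} says the opposite of the latter. This stands against treating removal as certain. It does not resolve the conflict, because no section links rejection to the PPS or retains these participants in the FAS.

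**Missingness need not depend on the unseen outcome.** A reader might call the data missing not at random by construction. That is not shown: several grounds are surgical, and the primary model includes surgical and anaesthesia duration, fluid volumes and centre. It remains plausible for non-completion, related AEs and missing gases.

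**Imputation details usually sit in the SAP, and a FAS requiring one assessment is conventional.** True in general. Here, however, the article itself fixes complete-case analysis and that FAS, beside a claim that everyone is analysed.

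**Conclusion.** The point holds as a contradiction within the Protocol article. The rejection list, the AE withdrawal ground, the FAS condition and the dropping of missing primary values cannot all be applied together with an intention-to-treat analysis of all participants. It should be settled before unblinding, because it decides who is in the primary analysis.

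Bias is possible but not demonstrated. It needs unequal removal between arms, or removed participants who differ between arms; equal removal of similar patients gives none. The shifts of 5.3 and 7.8 mmHg rest on an assumed 5-point imbalance and an assumed 100 mmHg gap (100/74 = 1.35 SD). They show only that a modest imbalance could reach or exceed the SE of 5.0 mmHg and use up 38% to 56% of the 14 mmHg beyond the margin (5.3/14 and 7.8/14). They should not be read as estimates for this trial.

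**What to change.** 1. State that the rejection criteria and withdrawal for an intervention-related AE do not remove a randomised participant from follow-up or from the FAS. Collect 48-h, 7-day and 30-day data unless consent is withdrawn or a study procedure is judged harmful. Use these grounds only to define the PPS.
2. Define the FAS as all randomised participants or, named as modified intention to treat, all randomised participants who had surgery. Drop the efficacy-assessment condition in either case.
3. Keep the complete-case primary analysis only together with a prespecified sensitivity analysis: multiple imputation by arm with a delta-adjusted tipping point. Do not assign a low value to ventilated participants, since their index can be measured.
4. As wording only, express the ICU-intubation and 2 h criteria as planned and expected, in line with Recruitment {15}.

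This reconciles Eligibility criteria {10}, Withdrawal from study, Analysis sets and {20c} without changing any clinical stopping rule. N stays at 1098.

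The cost is wording and modest analysis work, since visits to day 7 and telephone follow-up to day 30 are already planned. Including complicated cases may enlarge the SD slightly and dilute the effect somewhat. The estimated end date is 31 December 2025; if enrolment has ended, changes to eligibility wording come late and data on rejected participants may be incomplete. In that case, report their number and reasons by arm; items 2 and 3 can still be fixed before unblinding.

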### Who will take informed consent? {26a}

A trained research team will recruit participants and use standard randomization procedures, to assign them to the study population on the preoperative day.

### Additional consent provisions for collection and use of participant data and biological specimens {26b}

Not applicable. The preoperative signed informed consent form thoroughly informed the patient about the planned arterial blood sampling and obtained their consent.

## Interventions

### Explanation for the choice of comparators {6b}

Both 40% and 80% FiO2 are widely used in clinical anesthesia. However, there is currently no definitive conclusion regarding their respective benefits in reducing postoperative pulmonary complications in elderly patients. The study will comprise two cohorts, the “L” and “H” cohorts, to receive low FiO2 (40%) and high FiO2 (80%), respectively. Interventions will be performed as per the clinical practices established at either the national or local levels in China. The trial flowchart is shown in Fig. 1.

### Intervention description {11a}

Preoperatively, the participants in both cohorts will fast for 8 h and not use any sedatives or analgesics. On arrival at the ward/operating room, the data will be verified, and standard monitoring of the systolic and diastolic blood pressure, mean arterial pressure, pulse rate, electrocardiogram, blood oxygen saturation, entropy index, or bispectral index (BIS) will be conducted. Simultaneously, venous access will be obtained and maintained at a rate of 10–20 mL/kg/h. The total fluid volume will not exceed 50 mL/kg, to ensure intraoperative hemodynamic stability.

Intraoperatively, the same protocol will be used for anesthesia induction: etomidate 0.3 mg/kg or propofol 1.5–2 mg/kg, sufentanil 0.3–0.5 μg/kg, cisatracurium besylate 0.2 mg/kg, or rocuronium bromide 1 mg/kg, respectively. Anesthesia methods, including combined intravenous and inhalation anesthesia, total intravenous anesthesia, inhalation anesthesia, and reasonable use of vasoactive drugs, can be used intraoperatively.

The ventilator will be connected to the participant after a successful tracheal intubation. All participants will be ventilated using lung-protective ventilation, which includes VCV, PCV, and PCV-VG.

The tidal volume will be set at 6–8 mL/kg, which has been calculated, based on the ideal body weight, using the following formulae:For males: 50 + 0.91 × [height (cm)—152.4].For females: 45.5 + 0.91 × [height (cm)—152.4].

Moreover, the positive end-expiratory pressure (PEEP) and inspiratory/expiratory ratio will be maintained at 6–8 cm H2O and 1:2, respectively, with regular lung recruitment maneuvers. The ventilation rate will be adjusted, according to the intraoperative end-expiratory carbon dioxide, which will be maintained at 35–50 mm Hg.

The depth of anesthesia will continuously be adjusted, according to the entropy index, BIS value, or minimum alveolar concentration (MAC) value of the end-expiratory anesthetic gas. The entropy index and BIS value or MAC value of the end-expiratory anesthetic gas will be maintained at 40–60 or 0.7–2.6, respectively.

Intraoperative and perioperative information, adverse events (AEs), and serious adverse events (SAEs) will be recorded. Perioperative data includes the duration of the anesthesia and surgery, use of different types of anesthetics, volumes of fluids administered intraoperatively, and administration of postoperative analgesics and anticholinergic drugs.

The endotracheal tube will be removed in the operating room. If an endotracheal tube is inserted in the PACU, the ventilator parameters in the PACU should consistently be set intraoperatively, and the endotracheal tube should be removed after rapid recovery of spontaneous breathing. Both cohorts will be given Venturi masks for oxygen inhalation post-extubation, and the FiO2 will be set at 24%–40%. The initial setting will be at 24%. If clinical requirements are not met, the FiO2 will be increased to 40%, as needed. The FiO2 and duration of oxygen inhalation will be recorded.

After returning to the ward, the participants will decide whether to receive supplemental oxygen, based on their present condition. If oxygen is required, a Venturi mask will be used. The total time and concentration of oxygen inhalation will be recorded. Each site can use multimodal analgesia, as per the current condition.

During the postoperative monitoring period, evaluations will be conducted, and data will be documented for both the primary and secondary outcome measures.

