## Assignment of interventions: blinding

### Who will be blinded {17a}

Due to the nature of the study, anesthesiologists will not be blinded to the intervention protocol. Trial participants, outcome assessors, and data analysts will be blinded. To reduce potential bias, data collectors will be divided into two different teams: (1) anesthesiologists on duty in the operating room on the same day, in addition to postanesthetic care unit (PACU) staff, who will participate in the calculation and evaluation of the results, and (2) blinded principal investigator (PI) and co-investigator, statistician, and data collection and outcome evaluation personnel, which includes those who will provide care and evaluate participants in the ward pre- and postoperatively.

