## Statistical methods

### Statistical methods for primary and secondary outcomes {20a}

The oxygenation index data for the two cohorts will be collected, based on a preliminary experiment. The oxygenation index values will be presented as means and standard deviations.

The Student’s *t*-test will be used to assess the disparities between the two cohorts for continuous outcome variables adhering to a normal distribution. In cases of non-normal distribution, the Mann–Whitney test will be used. Categorical data will be analyzed, using the chi-squared or Fisher’s exact tests. These tests are one-sided, and statistical significance will be set at *p* < 0.025. The parameters will be computed and displayed, including approximations and a 97.5% confidence interval.

The primary and secondary outcome indicators will be evaluated using linear and generalized linear mixed-effects models.

A linear mixed-effects model was employed to analyze the primary outcome measures (oxygenation index and quantitative variables). The model included patient baseline data (age, gender, BMI, and prior SARS-CoV-2 infection history), intraoperative characteristics (anesthesia duration, intraoperative crystalloid volume, intraoperative colloid volume, surgical duration, surgical position, pneumoperitoneum pressure, intraoperative PEEP, occurrence of pulmonary re-expansion, intraoperative ventilator tidal volume, and airway platform pressure), and center and group factors.

For quantitative secondary outcome measures—including postoperative PACU oxygen duration, 24-h and 48-h oxygen therapy duration, and postoperative blood gas parameters (pH, partial pressure of carbon dioxide, and lactate) at 48 h—linear mixed-effects models were employed. The model included patient baseline characteristics (age, gender, BMI, and prior SARS-CoV-2 infection history) and intraoperative parameters (anesthesia duration, intraoperative crystalloid volume, colloid volume, surgical duration, surgical position, pneumoperitoneum pressure, intraoperative PEEP, occurrence of pulmonary re-expansion, and ventilator tidal volume), along with center and group factors.

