For qualitative data of secondary outcomes—including postoperative PACU oxygenation rate, 24-h postoperative oxygenation rate, 48-h postoperative oxygenation rate, pulmonary complications at 7 days postoperatively, and 30-day mortality rate—generalized linear mixed-effects models were employed. The model included patient baseline data (age, gender, BMI, and history of SARS-CoV-2 infection), intraoperative characteristics (anesthesia duration, intraoperative crystalloid volume, intraoperative colloid volume, surgical duration, surgical position, pneumoperitoneum pressure, intraoperative PEEP, occurrence of pulmonary re-expansion, intraoperative ventilator tidal volume, and airway platform pressure), and center and group factors.

For ordinal outcomes such as postoperative PACU oxygen concentration, 24-h postoperative oxygen concentration, 48-h postoperative oxygen concentration, and severity of pulmonary complications, a generalized linear mixed-effects model was employed. The model included patient baseline data (age, gender, BMI, history of SARS-CoV-2 infection), intraoperative characteristics (anesthesia duration, intraoperative crystalloid volume, intraoperative colloid volume, surgical duration, surgical position, pneumoperitoneum pressure, intraoperative PEEP, occurrence of pulmonary re-expansion, intraoperative ventilator tidal volume, and airway platform pressure), and center and group factors.

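### Mask oxygen after extubation is stepped up and stopped without a criterion, by staff outside the team called blinded, yet PACU oxygen concentration and duration are compared between cohorts

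*Protocol article*

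**What the plan says.** Intervention description {11a} fixes the device (Venturi mask), the range (24% to 40%) and the starting value (24%) for mask oxygen after extubation, identically in both cohorts. The next step is left open: "If clinical requirements are not met, the FiO2 will be increased to 40%, as needed". The clinical requirements are not defined. For the end of oxygen therapy the section states only that "The FiO2 and duration of oxygen inhalation will be recorded".

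Who will be blinded {17a} states that "anesthesiologists will not be blinded to the intervention protocol". It then describes two teams. The first is "anesthesiologists on duty in the operating room on the same day, in addition to postanesthetic care unit (PACU) staff". The second is the "blinded principal investigator (PI) and co-investigator, statistician, and data collection and outcome evaluation personnel", together with those who care for participants on the ward. The word blinded is attached only to the second team.

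The Secondary outcomes list includes the time of oxygen inhalation and the inspired oxygen concentration. Statistical methods {20a} models the quantitative outcomes "including postoperative PACU oxygen duration, 24-h and 48-h oxygen therapy duration" with a group factor, and does the same "For ordinal outcomes such as postoperative PACU oxygen concentration".

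**The concern.** The decision to move from 24% to 40% determines PACU oxygen concentration, and the decision to stop determines PACU oxygen duration. Both are made after allocation, and the natural reading is that the first team makes them. Suppose someone who knows a participant had 80% oxygen in theater reacts at a different saturation than for a participant who had 40%. The resulting difference in mask settings would be reported as an effect of intraoperative FiO2, although it reflects staff behavior. It could create a difference where none exists, or cancel a real one.

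The planned safeguards do not reach this. Randomization balances participants before the decision is made. Analysis by randomized cohort keeps the staff-made difference in the estimate. Blinded analysts see only the result. The covariates listed in {20a} do not include saturation at the time of an oxygen change.

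The point covers PACU oxygen concentration and PACU oxygen duration only. It does not cover the primary outcome at 48 h, the ward oxygen outcomes, or the PACU oxygenation rate, which the article does not define.

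**Working it through.** **Inputs from the protocol.** 439 per group before dropout, 20% dropout, one-sided α = 0.025, power 80% (Sample size {14}); one-sided tests at p < 0.025 and chi-squared tests for categorical data ({20a}).

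**The plan's own figure.** The pilot difference is 384 − 340 = 44 mmHg. Less the margin of 30, this leaves 14. With SD 74:

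n = 2 × ((1.960 + 0.842) × 74 / 14)² = 438.6, so 439 per group.

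439 / 0.80 = 548.75, so 549 per group and 1098 in total. Both stated figures reproduce, and 439 is used below.

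**Assumptions.** The protocol gives no step-up rate, no size for a staff-made gap and no direction. I took a rate of 10% to 50% in the lower cohort and a gap of 3 or 5 percentage points. Step-up is treated as yes/no (24% or 40%), which simplifies the ordinal mixed model planned in {20a}.

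**Formulas.** For rates p and p + d, with mean p̄:
- SE₀ = √(2 p̄(1 − p̄)/439)
- SE₁ = √((p(1 − p) + (p + d)(1 − p − d))/439)
- Smallest gap significant by itself: d = 1.96 × SE₀
- Probability of a significant result: Φ((d − 1.96 × SE₀)/SE₁)

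Worked case, p = 10% and d = 5 points: SE₀ = 0.02232, SE₁ = 0.02226, and (0.05 − 1.96 × 0.02232)/0.02226 = 0.28, so Φ = 0.61.

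**Staff-made gap in the tested direction, no true effect**

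| Lower-cohort rate | Smallest significant gap (points) | P(significant), 3 points | P(significant), 5 points |
|---|---|---|---|
| 10% | 4.3 | 0.29 | 0.61 |
| 20% | 5.6 | 0.19 | 0.43 |
| 30% | 6.2 | 0.16 | 0.35 |
| 50% | 6.6 | 0.14 | 0.32 |

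The nominal rate is 0.025. With 549 per group the smallest significant gap is 3.8 to 5.9 points. A gap in the other direction makes a false positive rarer: 0.04% to 0.22% at 3 points, at most 0.03% at 5 points.

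**Masking.** Take a true difference with 80% power and let a staff-made gap work against it.

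| Lower-cohort rate | True difference with 80% power (points) | Power left, 3 points opposing | Power left, 5 points opposing |
|---|---|---|---|
| 10% | 6.4 | 0.35 | 0.10 |
| 20% | 8.1 | 0.44 | 0.20 |
| 30% | 9.0 | 0.47 | 0.24 |
| 50% | 9.4 | 0.48 | 0.26 |

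**Duration.** The protocol gives no SD, so the gap is in SD units. The smallest gap significant by itself is 1.96 × √(2/439) = 0.132 SD. A staff-made gap of 0.10 SD gives a significant result with probability 0.32 in the tested direction and 0.0003 in the other.

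**The case against.** The strongest reply is that a saturation target for mask oxygen is bedside detail, which a condensed article may leave to the full protocol or a site procedure. The article does state a structure common to both cohorts: same device, same start, same range, step-up only when needed. But it is not silent on the step itself. It states a rule, and that rule is discretionary. Elsewhere it does give a numeric trigger: {11b} uses a saturation below 94% for intraoperative rescue, in the L cohort only.

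Second, two links are not stated: that the first team adjusts the mask, and that PACU staff know the allocation. This stands. PACU staff are never called unblinded, and since extubation is planned in the operating room, many would not see the study ventilator setting. However, the anesthesiologists are expressly unblinded, the mask follows extubation in their presence, and nothing prevents disclosure at handover.

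Third, randomization is stratified by center and center is in the models, so differences in oxygen practice between sites are balanced. That is correct, but a gap within a site driven by known allocation remains.

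Fourth, the percentages rest on assumed gaps, and nothing in the protocol shows that such a gap exists. That also stands. The figures show how small a gap would matter, not that one has occurred.

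**Conclusion.** The point holds, as a low-priority improvement. The stated rule leaves two compared secondary outcomes to the discretion of staff who are not described as blinded, and no later analysis can separate that discretion from a treatment effect. If knowledge of the cohort shifted the step-up rate by 5 points in the tested direction, a null comparison would come out significant in 32% to 61% of trials. An opposing shift of that size would cut 80% power to between 10% and 26%. These figures assume a step-up rate of 10% to 50%, a yes/no simplification of the outcome, and that the staff setting the mask know the allocation. The size and direction of any actual gap are unknown.

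**What to change.** In Intervention description {11a}, set one saturation threshold with a minimum duration for going above 24%, and one for stopping oxygen, identical in both cohorts. The investigators should choose the values; 94%, the preoperative eligibility value in {10}, is one example. Allow a clinical override and record it, and record the saturation at every oxygen change. The override means the rule reduces staff influence without abolishing it, but its use in each cohort can then be seen.

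The cost is one or two sentences, one CRF field and a short briefing of PACU staff, with slightly less staff discretion.

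Trial status estimates an end on 31 December 2025. If recruitment has closed, report that the PACU oxygen concentration and duration comparisons rest on decisions by staff outside the blinded team, and interpret both as exploratory. That costs one sentence.
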